## Methods/design

This is an evaluator-blinded, randomized controlled superiority trial with two parallel groups, and a 1:1 allocation ratio, with an 8-week intervention period and outcomes measured at baseline, 8 weeks and 16 weeks as a follow-up evaluation. The first statistical comparison will be performed after 8 weeks of intervention.

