### Trial design

The evaluations will start in January 2020. After evaluation, participants will be randomly allocated to two evaluator-blinded groups: the treatment group (TG) and the control group (CG). The randomization.com program will be used to randomize the participants and stratification will be performed to ensure balance between the groups within two strata (Clinical, Etiology, Anatomical, Pathophysiology (CEAP) 2 and 3 and CEAP 4 to 6). A separate, blinded researcher will contact the participants by telephone to ensure allocation concealment during screening, consent and initial assessment. A study researcher responsible for implementation will apply the exercise program.

Patients in the TG will perform the exercise program as described in this protocol and will start 1 week after the initial evaluation. The patients in the CG will continue their usual treatments (medication use, compression stockings and medical guidance). After 8 weeks of intervention, the patients will be re-evaluated (using the same initial evaluation questionnaire) by the same blinded evaluator for each group. The primary outcomes will be calf-muscle endurance and QOL and the secondary outcomes will be exercise capacity, ROM electrical muscle activity, and cardiac output. A final reassessment will be performed 8 weeks after the re-evaluation, as shown in Figs. 1 and 2 (Standard Protocol Items: Recommendations for Interventional Trials (SPIRIT) Figure).

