### Sample size

The sample size will be calculated based on a pilot study with eight patients (four patients in each group) using a multivariate analysis of variance (manova) test with repeated measures, within-between interaction with two groups and two measurements by analyzing calf endurance and the standard deviation of the number of repetitions from the pilot study. A two-tailed alpha error of 0.01 will be considered with a power of 80% considering clinical improvement for subjects with chronic venous disease after the supervised exercise protocol. The effect size will be calculated at the end of the protocol considering the number of repetitions of the calf-endurance test of all study participants. Moreover, considering a 20% loss to follow-up and 5% missing data, the number of participants will be increased by at least 20% based on sample size. The GPower (Germany) version 3.1 program will be used for statistical analysis.

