The statistical analysis will be performed using the GraphPad Prism version 5.0 statistical package software (GraphPad Software Inc., San Diego, CA, USA). The results of patient baseline characteristics and outcome variables (both primary and secondary) will be summarized using descriptive summary measures: expressed as mean (standard deviation) or median (range) for continuous variables and *n* (%) for categorical variables. The sample normality will be tested by the Shapiro-Wilk test. Treatment effects or differences between the study groups for primary and secondary outcomes will be analyzed by linear mixed model for group (usual care versus intervention) and time (baseline, 8 weeks and 12 weeks). As linear mixed models use all available data at each time point, no missing data imputation will be performed. Age and body mass index (BMI) will be included as covariates by adding them to the regression model. The clinical classification CEAP will be included as covariate if randomization imbalance occurs. The analyses will be based on the intention-to-treat principle, including data of all randomized participants with at least one outcome measure. The significance level will be set at 95% (*p* < 0.05). All participants will be included in the analysis of the original groups following the Consolidated Standards of Reporting Trials (CONSORT) recommendations.

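### CEAP stratifies the randomisation but enters the model only if imbalance occurs, so it will probably be left out; under some conditions the tests are then conservative

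*Protocol article*

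**What the plan says.** Under Trial design, the protocol article says that "stratification will be performed to ensure balance between the groups within two strata", the strata being CEAP "2 and 3 and CEAP 4 to 6". Under Methods/design it describes "two parallel groups, and a 1:1 allocation ratio". No block size or other restriction within strata is given.

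The statistical analysis paragraph (under Data collection, management and analysis) has outcomes "analyzed by linear mixed model for group (usual care versus intervention) and time (baseline, 8 weeks and 12 weeks"). Two covariates are unconditional: "Age and body mass index (BMI) will be included as covariates by adding them to the regression model". CEAP is conditional: "The clinical classification CEAP will be included as covariate if randomization imbalance occurs". Imbalance is not defined, and no other section puts the CEAP stratum in the model.

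**The concern.** A factor important enough to stratify on is normally kept in the analysis, because balancing on it changes the sampling variation of the treatment contrast. Here the order is reversed. Age and BMI, on which nobody stratified, are always in the model, while the stratification factor waits for an event that stratification is meant to prevent.

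Three things follow:

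- The factor will probably be dropped. If it is prognostic, the model then leaves between-stratum variance in the residual although the design has removed it from the contrast. Confidence intervals are too wide and power is lost.
- Which model is fitted depends on a judgement about observed balance.
- The conditional sentence names the clinical classification, while randomisation used two grouped strata. These may be different variables.

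Power matters here because the sample size will rest on a pilot of eight patients.

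**Working it through.** The plan gives no sample size, effect size or SD, so there is no figure of its own to reproduce. How strongly CEAP predicts the outcomes is not given either; the values of R² below are assumptions.

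**Formula.** Let R² be the share of the variance of the analysed contrast that the CEAP stratum explains, with allocation balanced within strata. The true standard error is proportional to √(1 − R²), but a model without the stratum reports one proportional to 1.

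- Inflation of the standard error = 1/√(1 − R²)
- Actual two-sided error at nominal 5% = 2 × [1 − Φ(1.96/√(1 − R²))]

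Results:

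- R² = 0.10: 1/√0.90 = 1.054. Then 1.96 × 1.054 = 2.066, and the error is 0.039.
- R² = 0.20: 1/√0.80 = 1.118. Then 1.96 × 1.118 = 2.191, and the error is 0.028.

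**Simulation check.** 4,000 trials per setting. All inputs are assumed: N = 60, half the patients in each stratum, permuted blocks of 4 within stratum, within-patient correlation 0.6, two-sided 5%. Power is for a 0.75 SD effect. The week-8 contrast between groups gave:

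| Variance explained | Model / true SE, stratum omitted | Type I error, omitted | Type I error, included | Power, omitted → included |
|---|---|---|---|---|
| 10% | 0.257 / 0.246 | 0.038 | 0.052 | 82% → 85% |
| 20% | 0.258 / 0.226 | 0.025 | 0.045 | 83% → 89% |
| 30% | 0.258 / 0.215 | 0.016 | 0.048 | 86% → 93% |

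**Change from baseline**, as a stand-in for the group-by-time term:

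- CEAP effect equal at both visits: it cancels. Type I error was 0.049 to 0.055 with or without the stratum.
- CEAP effect at follow-up only: omission is again conservative, with type I error 0.038, 0.023 and 0.014 for 10%, 20% and 30% of follow-up variance. Power was 90%, 90% and 91%, against 92%, 94% and 97% with the stratum.

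**Simple randomisation within strata.** The mismatch disappears: type I error was 0.054 without the stratum, with model SE 0.259 against true SE 0.258. Including the stratum still lowered the true SE to 0.231, so precision is gained even there.

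**How often the condition would be met.** Taking imbalance as chi-square p < 0.05 for stratum by arm (an assumption), it occurred in 0 of 4,000 trials in each blocked setting and in about 5.5% under simple randomisation.

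**The case against.** The strongest objection is that the planned analysis may not be exposed at all. The model is longitudinal with baseline as a time point, the abstract defines the primary outcomes as changes, and the Sample size section is built on an interaction of group with repeated measurement. These favour reading the effect from group-by-time, where a CEAP effect that is constant over time cancels. This stands as a limit on the size of the problem. It does not remove the point: the analysis paragraph names group and time without naming the interaction as the treatment-effect term, and nothing shows that the CEAP effect is constant.

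Second, blocking is not stated, and without some restriction within strata the reported standard error is correct. This also stands, although stratifying to secure balance achieves that aim only with some restriction.

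Third, the conditional sentence may mean the full clinical class (C2 to C6). Two broad strata do not balance C2 against C3, or C4 against C6, so the condition could then be met. A reader might infer that it will almost never be met; the text makes omission of the stratum likely but does not establish that.

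Fourth, a threshold for imbalance could sit in an analysis plan that is not shown, and balance can be checked without outcome data, so there is little room for result-driven choice. Granted. But the conditional rule itself is stated in the protocol, and a threshold elsewhere would not bring the model into line with the design.

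**Conclusion.** The point holds as a mismatch between a stated analysis rule and the design. The stratification factor will probably be left out, the model depends on an undefined check of balance, and the CEAP variable is ambiguous.

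The numerical consequence is conditional. With allocation restricted within strata, and CEAP explaining an assumed 10% or 20% of the variance of the analysed contrast, the 5% and 12% inflation of the standard error applies. In the assumed week-8 setting with N = 60, the loss of power is about 3 and 6 percentage points.

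A reader might infer that the standard errors and p-values are bound to be wrong. The documents do not support that, given the two situations in which the mismatch is nil. Nor is there a risk of excess false positives: where there is an error, it is conservative. This is a worthwhile correction at almost no cost, not a threat to the validity of a positive result.

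**What to change.** Replace the conditional sentence with: 'CEAP stratum (2-3 versus 4-6), as used at randomisation, will be included as a fixed effect, with its interaction with time, in all models regardless of observed balance.' Delete the imbalance condition. The interaction with time is needed because a main effect alone does not fully account for a CEAP effect that differs between visits.

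The cost is one sentence and a few degrees of freedom: one for the two-level stratum and two for its interaction with three time points. CEAP class is already recorded at the initial evaluation, so no new data are needed.

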## Discussion

Several observational studies have reported that participants with CVI have inadequate calf-muscle pumping [14]. Calf-muscle pumping is the primary mechanism to promote blood return from the lower limbs to the heart. During exercise, the calf muscles (gastrocnemius and soleus) contract and compress the deep intramuscular veins which increases venous pressure and increases blood flow from the deep venous system to the heart. This efficacy of this mechanism depends on talocrural mobility, venous competence, and the contraction strength of the calf muscles [14].

Studies have shown the physical and QOL benefits of exercise therapy for patients with CVI. Despite positive results, this training modality is not widely used for this population. Few researchers have shown the beneficial effects of different supervised or domiciliary exercise modalities on specific parameters such as improved calf-muscle pumping [13–15], increased mean peak torque [13], improvement in disease severity [17], increased ankle-joint movement [14], and improved calf-muscle resistance [15]. The authors believe that the study results will promote preliminary evidence to help health professionals indicate, prescribe and execute supervised exercises for treating symptoms in participants with CVI.

## Trials status

Protocol version

8 July 2019 – version 1.

The first patient will be recruited in January 2020.

The last patient will be recruited in May 2020.

## Data Availability

Data-sharing is not applicable to this article as no data sets were generated or analyzed during the current study.

## Abbreviations

ABI: Ankle-brachial index
ACSM: American College of Sports Medicine
CG: Control group
CVI: Chronic venous insufficiency
PAD: Peripheral arterial disease
ROM: Range of motion
SEM: Superficial electromyography
ST6: Step test 6
TG: Treatment group
VED: Vascular echo-Doppler
